### Ethics Approval

FAMILIA was reviewed and approved by the Indiana University institutional review board and the VA research and development committee (IRB #12794).

## Results

### Participant Involvement in the Research Design

The FAMILIA research team consulted with the VA Health Services Research & Development Service Pain/Opioid Consortium of Research Veteran Engagement Panel facilitation team and outlined a plan for how the panel can inform this project. The panel group includes 12 veterans from across the country who serve as patient advisors to researchers to enhance patient-centered research. All panel members have personal experience with chronic pain or opioids. Veteran members are a diverse group of men and women across a wide age range and include students, retirees, and current workers with varied military, volunteer, and professional experiences. Panel members provided patient-centered feedback that helped inform the study recruitment materials, study design, and anticipated feasibility issues.

### Preliminary Data

Members of the research team conducted a single-arm study of 8 veterans with chronic pain to develop and pilot the telehealth MI intervention proposed for FAMILIA. Qualitative data were collected regarding the accessibility and feasibility of virtual delivery and the outcome measures of pain, depression, and anxiety. Findings from this small pilot study helped refine the music imagery intervention and its delivery for FAMILIA. For example, owing to some veterans’ lack of technology skills, a technology questionnaire was added to the eligibility screening.

### Potential Results and Interpretations

There are several potential results and interpretations from the trial. It is expected that both music interventions will prove acceptable to veterans and that feasibility benchmarks will be reached. However, it is possible that one or both music interventions will not be embraced by all participants or may not meet all specified benchmarks. The qualitative interviews will identify the range of participant perceptions and experiences of both interventions and provide insight into the reasons for unacceptability or feasibility concerns. Although it is hypothesized that both music interventions will be more effective than usual care on pain and associated outcomes, differences in outcome scores may be observed but are unlikely to reach stochastic significance (because FAMILIA is not powered to evaluate efficacy). This potential scenario is acceptable in the context of pilot clinical trials where the primary objective is to field-test logistical aspects of the future RCT and to incorporate these aspects into the study design.

### Trial Status

FAMILIA received institutional review board approval in October 2021 and approval from VA Research and Development in November 2021. Recruitment began in March 2022 and as of July 2022, a total of 16 participants were enrolled.

## Discussion

The primary purpose of FAMILIA is to examine the feasibility and acceptability of a multicomponent interactive intervention (music imagery) and a single-component, minimally interactive listening intervention (music listening). FAMILIA is not powered to evaluate efficacy, but we anticipate that the music interventions will have a greater effect on outcomes compared with usual care.

### Strengths and Limitations

FAMILIA not only addresses the limitations of prior research but also responds to important clinical and research initiatives to develop and test safe and effective nonpharmacological interventions for chronic pain. In clinical practice, analgesics are widely used for pain, but suboptimal pain relief is common as are the side effects. Adverse events related to analgesics, especially nonsteroidal anti-inflammatory drugs and opioids, are well known. Given the modest benefits of analgesics and their safety concerns, novel nonpharmacological options are needed to reduce clinician and patient reliance on analgesics and to reduce the enormous burden of chronic pain on patients.

We selected an active comparator (music listening) to inform whether the design of the subsequent RCT should be a comparative effectiveness trial. We also designed FAMILIA to include a usual care control rather than other comparator options (eg, wait-list control or attention control). A usual care control group is appropriate given the paucity of studies and limited efficacy data of music interventions for chronic pain, especially for virtually delivered interventions. The study sample was drawn from a single VA medical center and may not be representative of all patients with chronic musculoskeletal pain.

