### Study Innovation

The FAMILIA (Feasibility and Acceptability of Music Imagery and Listening Interventions for Analgesia) study addresses four limitations in music intervention research for chronic pain: few studies in veterans, evaluation of multicomponent music interventions, methodological rigor, and virtual delivery. Most previous studies described a passive, one-session, single-component music listening experience for patients with acute pain [9-13]. In contrast, the FAMILIA study will evaluate 2 music interventions in veterans. Compared with music listening, less is known about multicomponent music interventions, which we hypothesize are more robust in reducing pain owing to greater treatment intensity and more frequent interactions with a music therapist. The FAMILIA study will assess outcomes (feasibility, acceptability, pain, and associated outcomes) of a single-component, minimally interactive intervention (music listening) and a multicomponent, interactive intervention (music imagery).

Systematic reviews of music interventions for pain cite a lack of methodological rigor because of poorly described interventions, a lack of theoretical foundation, and no reporting of adverse events [27,28]. The FAMILIA study will address these methodological concerns in several ways. First, we will adhere to reporting guidelines for music-based interventions developed by Robb et al [29]. Second, we will use a theoretically based conceptual framework (Figure 1) to explore the hypothesized mechanism of action and outcomes. Third, we will systematically monitor for specific potential adverse events in both interventions.

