**Aims and Questions**
Study aim 1: test the feasibility and acceptability of a multicomponent, interactive music imagery intervention and a single-component, minimally interactive music listening intervention.What percentage of veterans consent to study participation, attend intervention sessions, and complete the treatment protocol and scheduled outcome assessments?What are veteran experiences with both interventions?What aspects of the interventions do veterans perceive to be most or least helpful and most or least liked?What are barriers and facilitators to study participation?How did the music interventions compare to other chronic pain treatments already tried?Study aim 2: explore the effects of both music interventions (music imagery and music listening) vs usual care on pain and associated patient-centered outcomes.What are the changes from baseline to follow-up assessments (1, 3, and 4 months) on pain and associated patient-centered outcomes?What are the changes in proximal and distal mediators, and do they vary based on group assignment?What proportion of veterans achieve a clinically meaningful change in pain intensity and pain interference?

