#### Music Listening Group

In the music listening arm, a music therapist will meet with the veteran once to identify musical tastes, preferences, and activities; musical memories and social influences; and relationships between music, health, and quality of life [42]. From this meeting, an electronic playlist will be compiled for the veteran to listen to during the 12-week treatment period. The veteran will be asked to maintain a music listening log, including how long they listen, what they listen to, and any reactions to the music (eg, benefits and triggers). Music listening time will not be prescribed, but participants will be encouraged to keep track of their listening to music during the week. Our rationale for including the music listening intervention is to explore whether there is a clinically meaningful change in measures and perceived benefits from a less interactive, less intensive music intervention.

A member of the research team will check in with music listening participants (weekly for the first 3 weeks following their initial session, then biweekly following the 1-month assessment [approximately 7 check-ins in total]) to monitor safety, adherence (ie, time listening to music), and identify other issues.

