
### Data Analysis

As an RCT, it is expected that baseline characteristics of the study participants will be balanced across the 3 treatment groups; however, possible group imbalances will be assessed. Outcomes (feasibility, acceptability, pain, and other patient-centered outcomes) will be reported as means with SDs for continuous variables, or medians (IQRs) for nonlinear data and frequencies with percentages for categorical variables. Changes in pain, associated patient-centered outcomes, and proximal and distal mediators will be explored from baseline to follow-up assessments (1, 3, and 4 months). Bivariate analyses will be performed first to determine if there are significant differences in the 3 treatment groups for the antecedent, mediator, and outcome variables, which will also help to determine if there are group imbalances as discussed above. These analyses will be performed using ANOVA and chi-square tests for continuous and categorical variables, respectively. No post hoc *P* value adjustments will be made, as this is a feasibility study. Data transformations will be used if necessary and Fisher exact test will be used instead of chi-square when expected cell counts are small, with data analyses being performed using SAS software (version 9.4; SAS Institute [60]). Path analyses will then be performed to examine the path coefficients for the entire conceptual study model (Figure 1). The path coefficients, model fit indices, and covariance structures, along with the results from the bivariate analyses, will be used to determine model adjustments and parameter estimates necessary to determine the power for a larger full study. Path analyses will be performed using Mplus (version 8.7; Muthén & Muthén [61]).

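### Music listening is included to inform whether the next trial should be a comparative effectiveness trial, but Aim 2 names only comparisons with usual care, and the three-group test isolates neither those nor imagery versus listening

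*Protocol article*

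**What the plan says.** The protocol article describes the comparison between arms in several places.

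- **Purpose of the arm (Strengths and Limitations).** "We selected an active comparator (music listening) to inform whether the design of the subsequent RCT should be a comparative effectiveness trial".
- **Hypothesis (Study Innovation).** A sentence that sets multicomponent interventions beside music listening says of the former: "which we hypothesize are more robust in reducing pain owing to greater treatment intensity and more frequent interactions with a music therapist".
- **Second rationale for the arm (Music Listening Group).** To "explore whether there is a clinically meaningful change in measures and perceived benefits from a less interactive, less intensive music intervention".
- **Aim 2 (Textbox 1).** To "explore the effects of both music interventions (music imagery and music listening) vs usual care on pain and associated patient-centered outcomes". One key question adds "What are the changes in proximal and distal mediators, and do they vary based on group assignment", with no pair of arms named.
- **Analysis (Data Analysis).** Outcomes are summarised descriptively. Bivariate analyses are then run to "determine if there are significant differences in the 3 treatment groups for the antecedent, mediator, and outcome variables", and "These analyses will be performed using ANOVA and chi-square tests for continuous and categorical variables, respectively". No post hoc adjustment of P values is planned. Path analyses of the conceptual model follow.

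The Abstract, Potential Results and Interpretations, and the opening of the Discussion also frame effects as music versus usual care. The Abstract and the later sections say that the trial is not powered for efficacy or for differences in outcomes.

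**The concern.** Calling music listening an active comparator, and tying it to a possible comparative effectiveness trial, points to music imagery versus music listening. The hypothesis in Study Innovation gives that comparison a direction. No aim, key question or analysis statement names it.

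The three-group test does not fill the gap. It asks whether any arm differs from any other, so it does not isolate the Aim 2 contrasts either. If the plan is followed to the letter, the report can contain an overall P value and arm summaries, but no estimated difference with an interval for any pair of arms. Readers and the team planning the next trial would have to reconstruct the comparison or infer it from which results reached significance. In arms this small, patterns of significance are a poor guide to whether two interventions differ. Informing the next design is the declared product of this pilot, so its purpose and its analysis should match.

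**Working it through.** **1. Passages side by side.** Strengths and Limitations and Study Innovation imply imagery versus listening. Aim 2 names both music interventions versus usual care. Music Listening Group speaks of change with listening. Data Analysis specifies a test over three groups. Imagery minus listening is not named as an effect comparison anywhere in the article.

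**2. Arm sizes.** Study Design gives 60 participants at 2:1:1: 60 × 2/4 = 30 and 60 × 1/4 = 15, so 30/15/15 as stated. Aim 1 Outcomes expects 85% of outcome assessments to be completed: 0.85 × 30 = 25.5 and 0.85 × 15 = 12.75, rounded to 26/13/13.

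**3. Assumptions.** The article gives no alpha, SD or effect size. For illustration I take SD 1, two-sided 5% and an effect of 0.5 SD.

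**4. What the three-group test can tell.** Its power comes from a noncentral F distribution with noncentrality λ = Σ nᵢ(μᵢ − μ̄)², where μ̄ is the weighted mean. Arms are in the order imagery, listening, usual care.

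| True effects (SD) | Arms | μ̄ | λ | Rejection |
|---|---|---|---|---|
| 0.5, 0.5, 0 (imagery = listening) | 30/15/15 | 0.375 | 45 × 0.125² + 15 × 0.375² = 2.81 | 29% |
| 0.5, 0, 0 (only imagery works) | 30/15/15 | 0.25 | 30 × 0.25² + 30 × 0.25² = 3.75 | 37% |
| 0.5, 0.5, 0 | 26/13/13 | 0.375 | 39 × 0.125² + 13 × 0.375² = 2.44 | 25% |
| 0.5, 0, 0 | 26/13/13 | 0.25 | 26 × 0.25² + 26 × 0.25² = 3.25 | 33% |

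The two situations differ in exactly the respect that matters for imagery versus listening, yet the rejection rates are close. Neither a significant nor a non-significant overall result separates them.

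**5. What two separate tests against usual care can tell.** I simulated 26/13/13 with both music arms 0.5 SD better than usual care, so that imagery and listening are truly equal. Imagery versus usual care is significant in about 30.1% of trials, listening versus usual care in about 23.0%, and both in about 13.7%. The proportion with exactly one significant is 30.1 + 23.0 − 2 × 13.7 = 25.7, about 26%. Imagery alone is significant in 30.1 − 13.7 = 16.4%, and listening alone in 23.0 − 13.7 = 9.3%. The tilt towards imagery arises because that arm is twice as large.

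**6. Precision if the contrasts are named.** The half-width of the 95% confidence interval, in SD units, is t(0.975, N − 3) × √(1/n₁ + 1/n₂).

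- Imagery minus listening, 30 vs 15: 2.002 × 0.316 = 0.63. At 26 vs 13: 2.010 × 0.340 = 0.68.
- Imagery minus usual care: the same arm sizes, so also 0.63 and 0.68.
- Listening minus usual care, 15 vs 15: 2.002 × 0.365 = 0.73. At 13 vs 13: 2.010 × 0.392 = 0.79.

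Imagery minus listening is therefore as precise as imagery versus usual care and more precise than listening versus usual care. Precision gives no reason to leave it out, but all three intervals are wide.

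**The case against.** A reader might infer that the choice of the next trial would rest on comparisons that do not address it. The article does not support that.

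- The three-group analysis includes both music arms. If means and SDs are reported by arm, imagery minus listening and its interval can be derived.
- Aim 1, the primary purpose, collects feasibility data, treatment credibility for each music intervention, and interviews with at least eight participants from each music arm. All of this bears on whether listening would make a viable comparator.
- Listening versus usual care is itself relevant, because it indicates whether listening is a credible active comparator.
- Strengths and Limitations sets no rule based on efficacy. It says only that the arm helps inform the choice.
- Nothing in the article says that a null overall test will be read as similarity, or a split against usual care as superiority. Those misreadings are possible but conjectural.

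All of this stands, and it limits the point. It can also be said that pairwise contrasts usually belong in a statistical analysis plan and that the pilot is openly unpowered. That answers less. The article does state its aim, its hypothesis and its between-group test, and these do not match the purpose it gives the arm. An analysis plan faithful to Aim 2 would carry the mismatch forward. Low power favours estimates with intervals over a P value. It is not a reason to leave the contrast unnamed.

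**Conclusion.** The point holds as a modest mismatch between a stated purpose and the stated analysis, and it should be corrected. The article implies imagery versus listening in its rationale and hypothesis, names only comparisons with usual care in Aim 2, and specifies a test that isolates none of them. It does not follow that the design decision lacks relevant evidence, since the arm-level summaries and the Aim 1 data contribute.

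Under the assumed values, the three-group test rejects in about 25% of trials and the two comparisons with usual care split in about 26%, with imagery and listening truly equal. These percentages depend on the assumed 0.5 SD effect and 5% level, neither of which is in the article. The half-widths of 0.63 SD (all 60) and 0.68 SD (85% completion) depend only on the arm sizes and a common SD. The mismatch itself depends on none of these figures.

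**What to change.** **Aim 2 (Textbox 1) and Data Analysis.** Name three exploratory contrasts: imagery minus usual care, listening minus usual care, and imagery minus listening. Report each as an estimated difference with a 95% confidence interval, in place of relying on the three-group P value. Details such as outcome and time point can be left to the statistical analysis plan.

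**Strengths and Limitations.** After the sentence on the active comparator, add wording such as: The estimated difference between music imagery and music listening is expected to have a 95% confidence interval half-width of about 0.63 SD with all 60 participants, or 0.68 SD at 85% completion. It is too imprecise to settle the choice of design alone and will be read with the Aim 1 feasibility and acceptability results.

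**Cost.** A few sentences and one extra contrast from data already being collected, with no added patients, visits or measures. The small downside is that the interval for imagery versus listening will be visibly wide.

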### Conclusions

The long-term objective of this research team is to develop and test music interventions that improve chronic pain management and can be implemented in various clinical settings. Findings from FAMILIA will inform refinement of interventions and trial design in advance of conducting a fully powered trial to identify putative mechanisms and test efficacy.

## Appendix

Multimedia Appendix 1 External review report from grant funders.

## Abbreviations

BPI: Brief Pain Inventory
FAMILIA: Feasibility and Acceptability of Music Imagery and Listening Interventions for Analgesia
ICD 9/10: International Classification of Diseases 9th and 10th editions
PHQ-9: Patient Health Questionnaire-9
PTSD: posttraumatic stress disorder
RCT: randomized controlled trial
VA: Veterans Affairs
